## Study objectives

The ARES study has two primary objectives:To investigate whether aspirin regimens based on bid or three times daily (tid) administration of 100 mg result in a more complete suppression of platelet-derived TXA_2_ throughout the dosing interval, without significantly affecting in vivo PGI_2_ biosynthesis, as compared to the standard od regimen. Serum TXB_2_ will be measured as an index of platelet COX-1 activity, specifically reflecting the antiplatelet pharmacodynamics of aspirin (biochemical efficacy) (http://www.ema.europa.eu/docs/en_GB/document_library/Scientific_guideline/2009/09/WC500003340.pdf). A major urinary PGI_2_ metabolite, 2,3-dinor-6-keto-PGF_1alfa_ (PGIM) will be measured to assess the impact of different aspirin regimens on vascular COX-2 activity (biochemical safety)^32^. The comparison between aspirin 100 mg bid or tid vs. 100 mg od will test a superiority hypothesis in terms of serum TXB_2_ levels associated with each experimental vs. standard regimens. PGIM comparisons will assess the non-inferiority of any multiple daily dosing regimen vs. the standard od regimen. This objective will be addressed by a randomized, parallel-arm, double-blind, controlled study of 2-week aspirin treatment (part A) aimed at identifying the aspirin regimen to be further evaluated during long-term follow-up in the second part (part B) of the study.To evaluate the long-term persistence of superior biochemical efficacy of an optimized, multiple daily dosing regimen, as compared to the aspirin 100 mg od regimen. Biochemical efficacy will be assessed by repeated measurements of serum TXB_2_ (every 3 months over 20 months). A multiple daily dosing regimen will be tested for superiority vs. od dosing in terms of biochemical efficacy throughout the dosing interval, in an open-label, randomized study comparing aspirin 100 mg od vs. the optimal multiple daily dosing regimen identified in part A, with a follow-up of 20 months. This long-term follow-up will also provide an estimate of compliance with the experimental dosing regimen.

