### Part B

The experimental aspirin regimen associated with a significantly lower serum TXB_2_ level and non-inferior urinary PGIM excretion rate (i.e., ≤30% reduction) as compared to aspirin 100 mg od, will be selected for part B, and patients will be randomized in an open-label fashion to the standard vs. the optimized multiple dosing regimen for 20 months. The primary end point of part B will assess the long-term persistence of the superior biochemical efficacy of the optimized vs. standard aspirin regimen, in at least 6 out of 10 determinations of serum TXB_2_ that will be performed over 20 months. Secondary end points of part B will explore the following: (i) the safety of the experimental aspirin regimen, as reflected by any major bleeding and gastrointestinal symptoms considered attributable to aspirin; (ii) effectiveness in reducing MPN-specific symptom burden and pain attributable to microcirculatory disturbances; and (iii) stability over 20 months of the degree of platelet activation in vivo, as assessed by urinary TXM. The stability of TXM will be assessed in a subgroup of 150 patients.

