## Study end points and statistical analysis

The co-primary end points of part A are as follows: (1) platelet TXA_2_ production ex vivo, as reflected by serum TXB_2_, measured in samples collected in the morning, before the next aspirin intake; and (2) vascular PGI_2_ biosynthesis in vivo, as reflected by urinary PGIM excretion in a urine sample collected in the morning before the next aspirin intake. Urinary TXM excretion represents a secondary end point. These biomarkers will be measured at randomization and at 14 ± 2 days thereafter.

The primary end point of part B is represented by serum TXB_2_ measured 10 times in samples collected in the morning, before the next aspirin intake. The secondary end points are related to exploratory assessment of safety and tolerability of the experimental aspirin dosing regimen, and stability over time of in vivo platelet activation, as detailed above.

Based on previous findings^12,14^, we expect the mean ± standard deviation (SD) serum TXB_2_ in ET patients on aspirin 100 mg od and 100 mg bid to be 22 ± 33 and 5.0 ± 6.0 ng/ml, respectively. We plan to test with *α*-error of 0.05 and a *β*-error of 0.2 (power 80%) the following hypotheses:100 mg bid is superior to 100 mg od, with a ≥50% reduction in serum TXB_2_ (required sample size 70 patients/arm)100 mg tid is superior to 100 mg bid, with a ≥50% reduction in serum TXB_2_ (required sample size 70 patients/arm)

Anticipating a 30% dropout over the entire study duration, we plan to enroll 100 patients/arm to ensure adequate statistical power. For urinary PGIM, we expect the mean ± SD PGIM excretion rate in ET patients on aspirin 100 mg od to be 195 ± 119 pg/mg creatinine^33^. Using the above sample size (*n* = 70 patients/arm), the study has 80% power to test the hypothesis that any experimental treatment may reduce urinary PGIM to <140 pg/mg creatinine, i.e., by >30%. This threshold of PGIM inhibition vs. the standard dosing regimen can be considered reasonably safe based on the following considerations: urinary PGIM excretion is minimally affected by low-dose aspirin in healthy subjects^32,33^; in ET subjects, aspirin 100 mg bid did not significantly modify PGIM as compared to 100 mg od^33^; and this threshold corresponds to the intra-subject coefficient of variation on repeated measurements of PGIM excretion over time^39^.

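### PGIM is a non-inferiority co-primary with a 30% margin, but its power statement tests for a reduction and uses a cut-off of 140, which is a 28.2% fall

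*Protocol article*

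**What the plan says.** The Protocol article describes the PGIM comparison in three places.

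- *Study objectives* gives the general aim as more complete thromboxane suppression "without significantly affecting in vivo PGI_2_ biosynthesis". It then specifies the test: "PGIM comparisons will assess the non-inferiority of any multiple daily dosing regimen vs. the standard od regimen".
- *Part B* makes this a condition for selecting the regimen. Besides a significantly lower serum TXB2, the regimen must show a "non-inferior urinary PGIM excretion rate (i.e., ≤30% reduction) as compared to aspirin 100 mg od".
- *Study end points and statistical analysis* names PGIM as one of two co-primary end points of Part A. It assumes "195 ± 119 pg/mg creatinine" on the once-daily regimen and 70 patients per arm, and claims "80% power to test the hypothesis that any experimental treatment may reduce urinary PGIM to <140 pg/mg creatinine, i.e., by >30" per cent. The next sentence defends this threshold as reasonably safe.

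**The concern.** A non-inferiority test takes as its null hypothesis that the regimen lowers PGIM by the margin or more, and declares success by rejecting it. The power sentence makes a fall of more than 30% the hypothesis that the study is powered to test. That describes a test for detecting harm. Failing to detect harm is not the same as ruling it out, and the phrase about not significantly affecting prostacyclin points the same way.

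The figures within the sentence also disagree. On the stated mean of 195, a cut-off of 140 is not a 30% reduction, so the article carries two margins for one co-primary.

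The result helps decide which regimen is given for 20 months in Part B and is meant to inform the choice for a phase III trial. The hypothesis and threshold behind that decision should be stated once and in the right direction.

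**Working it through.** **Inputs.** From *Study end points and statistical analysis*: once-daily mean 195, SD 119, n = 70 per arm, cut-off 140, power 80%. From *Part B*: margin 30%. Assumptions: the same SD in both arms; alpha of 0.05, stated for the TXB2 hypotheses, also applies to PGIM and is two-sided (equivalent to one-sided 0.025). All results use the normal approximation.

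**Step 1: the cut-off.**
- (195 − 140)/195 = 55/195 = 28.2%.
- A 30% fall is 0.30 × 195 = 58.5, which gives 195 − 58.5 = 136.5.
- A regimen mean of 138 against 195 is a fall of 57/195 = 29.2%. It meets the Part B criterion but lies below 140.

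**Step 2: the stated power.**
- SE of the difference = 119 × √(2/70) = 20.11.
- Difference test, delta 55: Φ(55/20.11 − 1.96) = 78%, with 74 per arm needed for 80%.
- Difference test, delta 58.5: Φ(58.5/20.11 − 1.96) = 83%, with 65 per arm needed for 80%.
- With one-sided 0.05 the figures are 86% and 90%. The closest match to the stated 80% is delta 55, two-sided 0.05.

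**Step 3: the same design as a non-inferiority test.** Power = Φ((margin − true fall)/SE − 1.96).

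| True fall in PGIM | Margin 55 (cut-off 140) | Margin 58.5 (cut-off 136.5) |
|---|---|---|
| 0% | 78% | 83% |
| 5% (9.75) | 61% | 68% |
| 10% (19.5) | 42% | 49% |

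At zero true difference the formula is that of Step 2, so the results coincide. Away from zero, power falls quickly, and the article does not state which true difference it assumes.

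**Step 4: why the direction matters.** Take a regimen with a true 30% fall (58.5).
- If a non-significant difference test were read as safe, it would pass with probability 1 − Φ(58.5/20.11 − 1.96) = 1 − 0.83 = 17%. With one-sided 0.05 this is 10%.
- If the lower 95% confidence limit must exclude a fall of 58.5, it would pass 2.5% of the time, by construction.

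**Step 5: does the slip in the cut-off help a regimen pass?** Under the confidence-limit rule with margin 55, a true fall of 58.5 passes with probability Φ((55 − 58.5)/20.11 − 1.96) = 1.6%, which is below 2.5%. As a margin, 140 is the stricter of the two.

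**The case against.** The strongest reply is that the intention is plain and only one sentence is badly worded. *Study objectives* contrasts superiority for TXB2 with non-inferiority for PGIM, *Part B* repeats the term with its margin, and the threshold is defended in the way one defends a margin. The article condenses a full protocol, where the confidence-limit rule, the sidedness of alpha and the analysis scale may be set out. Their absence here is not a finding.

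Much of this stands, and it limits what may be concluded.

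- A reader might infer that the 80% is purely power to detect harm, or that the sample size is wrong. Step 3 shows that a non-inferiority calculation at zero true difference reproduces it about as well.
- A reader might infer that the slip in the cut-off lets an unsafe regimen through. Step 5 shows the reverse.
- A reader might take the 30% criterion in *Part B* as a bare point-estimate rule, under which a regimen at the margin would pass about half the time. The article does not say that the point estimate decides. It also does not say that non-significance counts as safe, so the 17% is conditional. The Scheffé procedure is named for serum TXB2 and not for PGIM.
- The figures use 70 per arm, but the 30% dropout covers the whole study and PGIM is read after two weeks. With all 100 per arm (SE 16.83), power at margin 58.5 would be 94% at zero difference and 64% at a true 10% fall, and the 17% would become 6%.

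What the reply does not remove is the conflict in the text. A fuller document cannot follow a hypothesis of reduction below 140 and a 30% non-inferiority criterion together.

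**Conclusion.** The point holds as a contradiction in the stated hypothesis and threshold. The PGIM co-primary is defined as non-inferiority with a 30% margin, while its power statement describes a test that PGIM is reduced beyond the margin and uses a cut-off equal to a 28.2% fall. Both are wrong as written and should be corrected before Part A data are analysed.

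The effect depends on how the wording is applied. At 70 per arm, a regimen with a true 30% fall passes about 17% of the time if non-significance is read as safe, against 2.5% under a confidence-limit rule. This rests on SD 119 in both arms and two-sided alpha 0.05. The documents do not show that an unsafe regimen would be selected or that 70 per arm is too few at zero true difference. The weakness in the power statement is its unstated true difference, because power drops to 49% or 42% at a true 10% fall.

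**What to change.** In *Study end points and statistical analysis*, replace the PGIM sentence with a non-inferiority statement.

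- Null hypothesis: the regimen lowers PGIM relative to once-daily dosing by at least the margin.
- Decision rule: declare non-inferiority only if the confidence limit for the regimen-versus-once-daily difference or ratio excludes the margin. State the confidence level and the sidedness of alpha.
- Margin: use one throughout, either 30% (136.5 on a mean of 195) or a cut-off of 140 (28.2%), and make *Part B* agree.
- Power: state it with its assumed true difference. At 70 per arm with a two-sided 95% interval, it is 83% (margin 58.5) or 78% (margin 55) at zero difference, and 49% or 42% at a true 10% fall.
- In *Study objectives*, align the phrase about not significantly affecting prostacyclin with the margin.

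A difference or a ratio will serve, and the article does not require the log scale. If a ratio is chosen, power must be recalculated: with log-normal data and the same coefficient of variation, a 30% margin gives 96% at zero difference and 75% at a true 10% fall.

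The cost is rewording and one recalculated power figure. The price is a stricter, explicit pass criterion and, on the raw scale, a less favourable power statement. No extra patients or samples are needed.

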The same 300 ET patients will be randomized in part B of the study that will test the long-term persistence of superior biochemical efficacy of the optimized vs. standard dosing regimen. In all, 112 patients/arm will be needed to assess with an *α*-error of 0.05 and 80% power, a reduction of at least 50% in serum TXB_2_ with the optimized regimen (100 mg bid or tid) vs. the standard aspirin regimen (100 mg od), in at least 6 out of 10 determinations performed over 20 months.

Differences in mean serum TXB_2_ values will be evaluated by one-way analysis of variance, using Scheffe multiple-comparison test to allow comparisons of the three different treatments in part A. Analysis of covariance using multiple regression with dummies for the different treatments will be used if, at single univariate analysis, major differences (*p* < 0.05) in the distribution of gender, age, platelet count, JAK2 mutational status, spleen size, aspartate aminotransferase, alanine aminotransferase, or creatinine, and type of cytoreductive drug (if any) will be present between the three treatment subgroups. Both intention-to-treat and per-protocol analyses will be carried out.

It can be reasonably anticipated that a portion of the ET patients recruited in this trial according to the 2008 WHO diagnostic criteria^4^ might fall into the category of the pre-PMF according to the revised 2016 WHO criteria^38^. In a large international study of 1104 ET patients, diagnosis was revised to pre-PMF in 16%;^40^ these patients have been reported having an increased tendency toward bleeding^41^. Therefore, we will perform a pre-specified secondary analysis in the group of patients who will develop major and/or non-major clinically relevant bleeding in comparison with the patients with an uneventful course. All the bone marrow biopsies of the recruited patients will be revised by an ad hoc committee formed by the pathologist of the Coordinating Center and the pathologist of the Center where the patient had been recruited in order to assess whether patients had a true-ET or a pre-PMF according to the revised WHO classification;^38^ both the pathologists involved in the bone marrow revision will be blinded to the clinical characteristics of the patients. If the pathologists will provide different opinions, we will consult with a qualified third pathologist. The incidence of pre-PMF in patients with bleeding events will be compared to that found in non-bleeders.

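### Part B is stated to need 112 patients per arm, but 300 patients less the protocol's own 30% dropout leave about 105 per arm by the end of the study

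*Protocol article*

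**What the plan says.** All of the sizing is in the Protocol article, section Study end points and statistical analysis.

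- **Enrolment.** Part A has three arms and needs 70 patients per arm. The protocol continues: "Anticipating a 30% dropout over the entire study duration, we plan to enroll 100 patients/arm". Three arms of 100 make the 300 patients.
- **Who enters Part B.** "The same 300 ET patients will be randomized in part B of the study". The section Part B adds that "patients will be randomized in an open-label fashion to the standard vs. the optimized multiple dosing regimen for 20 months", so there are two arms. No allocation ratio is given.
- **Part B size.** The requirement reads "In all, 112 patients/arm will be needed to assess". Alpha is set at 0.05 and power at 80%. The target is serum TXB2 lower by half or more on the selected regimen, in six or more of ten measurements over 20 months.
- **Planning values.** Mean ± SD serum TXB2 on the od and bid regimens is expected "to be 22 ± 33 and 5.0 ± 6.0 ng/ml, respectively". They are given ahead of the Part A hypotheses. No separate values are given for Part B.

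No dropout allowance is attached to the 112, and nothing says that 112 already contains one.

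**The concern.** The protocol makes one attrition assumption for the whole study and uses it once, to inflate the Part A requirement. The Part B requirement is then set against the same 300 patients without that assumption being applied. If the 30% is taken at its word, the number left at the end is below the number that the protocol says it needs.

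Part B carries the second of the two primary objectives (Study objectives). At stake is whether its stated 80% power agrees with the protocol's own loss assumption.

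**Working it through.** **Inputs**

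- Patients: 300. Loss over the whole study: 30%. Part A need: 70 per arm. Part B need: 112 per arm, so 224 in two arms. All are stated in Study end points and statistical analysis.
- Effect: a 50% reduction from the od mean of 22 ng/ml, so 22 versus 11, a difference of 11. The mean and the od SD of 33 are stated there.
- Assumed: 1:1 allocation, since the size is given as one number per arm. Sidedness and the SD used for Part B are not stated, so they are found by reproducing 112.

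**Step 1: reproduce 112.** For two means with a common SD,

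n per arm = 2 × (z_alpha + z_power)² × SD² / difference².

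One-sided alpha 0.05, 80% power, SD 33 in both arms:

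2 × (1.645 + 0.842)² × 33² / 11² = 111.3, rounded up to **112**. The t-test version gives 111.97.

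This contains no dropout allowance. The other combinations tried do not give 112. For example, a one-sided test with SD 33 in one arm and 16.5 or 6 in the other gives 70 or 58 per arm.

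**Step 2: reproduce the enrolment.** 70 / (1 − 0.30) = **100** per arm, × 3 = 300. This is the Part A requirement inflated for the whole-study loss.

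**Step 3: apply the same 30% to Part B.**

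- 300 × 0.70 = 210 patients; 210 / 2 = **105 per arm**.
- 112 − 105 = 7 per arm (7 / 112 = 6.3%), or 14 patients in all.
- Largest total loss that still leaves 224: 1 − 224/300 = **25.3%**.

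The 105 does not depend on when the losses occur, because the 30% is a total for the study.

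**Step 4: power on the basis that gives 112.** Power = Φ(difference / (SD × √(2/n)) − 1.645).

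- n = 112: Φ(2.494 − 1.645) = **80.2%**
- n = 105: Φ(2.415 − 1.645) = **77.9%**

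The cost is about 2 percentage points. The formula compares two means at one time point and does not model the six-of-ten rule.

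**The case against.** **105 is an end-of-study count.** The criterion concerns six of ten measurements, not the last visit, and patients who leave late supply earlier values. As an illustration, take 150 randomized per arm, ten evenly spaced measurements and steady loss reaching 30% at month 20. The number still in the study is then 150 − 45 × 6/10 = 123 per arm at the sixth measurement, 114 at the eighth and 105 only at the tenth. If the rule is applied visit by visit, eight of the ten measurements keep at least 112 per arm. This stands as a limit on the size of the problem. It does not remove it, because the timing of loss is an assumption, the article does not say whether the rule works by visit or by patient, and the 30% was applied in full when Part A was sized.

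**The inputs behind 112 are inferred.** This also stands. With the expected values the protocol does print (22 ± 33 versus 5.0 ± 6.0, a difference of 17), power at 105 per arm exceeds 99.9%. With a difference of 11 and SDs of 33 and 6, it is about 96% one-sided. Those inputs do not yield 112, however, so they cannot defend that number as the requirement.

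**Stronger readings that a reader might infer.**

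- *Part B is seriously underpowered.* The documents do not support this. On the basis that yields 112, the loss is about 2 points. The unstated sidedness of the test is a separate question from dropout.
- *Enrolment must rise to 112 / 0.70 = 160 per arm, 320 in all.* A change of this size in power does not call for that.
- *Nearly all of the loss falls in Part B, so Part A should be restated as well.* The protocol does not divide the 30% between the parts.
- *A repeated-measures analysis on the log scale would win the power back.* The article gives neither a within-patient correlation nor a log-scale variance, so this cannot be shown.

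**Conclusion.** The inconsistency is real and small. The protocol says that Part B needs 112 per arm, while its own enrolment and loss figures leave about 105 per arm at the end of the study. Reading 112 as already inflated for dropout has no support: the text presents it as the number needed for 80% power, and it reproduces without inflation.

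On the basis that reproduces 112, power is about 78% instead of 80%. It would be nearer to 80%, or above it, to the extent that the analysis uses measurements made before dropout. The conclusion assumes 1:1 allocation and that the 30% means patients lost by the end of the study. The power figures further assume a one-sided 0.05 test with SD 33 in both arms. The conflict between 112 and 105 needs only the first two assumptions.

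This is a conflict between printed figures, so neither the condensed format of an article nor a separate analysis plan explains it.

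**What to change.** Reconcile the Part A and Part B sizing paragraphs in Study end points and statistical analysis in one of two ways:

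1. Give Part B power at the expected 105 per arm, about 78% on the basis above, and state the sidedness, the difference and the SDs used; or
2. Keep 112 per arm and add that it is met only if total loss over the study stays at or below about 25% (224 of 300 patients retained).

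Under either option, state the allocation ratio and that 112 contains no dropout allowance. If the calculation behind 112 used other inputs, give those and recompute the power at 105.

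The cost is a few sentences. Enrolment, visits and design stay as they are. Under the first option the stated Part B power becomes slightly less favourable.

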Low-dose aspirin reduces by ≈25% the rate of major CV events, in a variety of high-risk clinical settings^21,24^. However, at variance with non-ET patients, a standard od regimen of low-dose aspirin administration is inadequate to fully inhibit platelet TXA_2_ production in ≈80% of ET patients^12,14,25^. A faster renewal of the drug target, due to enhanced megakaryopoiesis, is both biologically and pharmacologically plausible in ET^14,26^. Accelerated platelet turnover is associated with a higher-than-normal fraction of newly released platelets with unacetylated COX-1 and/or COX-2^12^, which would account for incomplete inhibition as well as partial recovery of TXA_2_-dependent platelet function during the 24-h dosing interval^9^. Two independent studies have shown that the duration of the antiplatelet effect of low-dose aspirin is shortened in the majority of aspirin-treated ET patients, and incomplete suppression of platelet TXA_2_ production during the 24-h dosing interval can be largely rescued by a twice daily (bid) low-dose aspirin regimen^14,25^. However, approximately one-third of a small group (8 of 22) of ET patients treated with aspirin 100 mg bid still had persistently high serum TXB_2_ values^14^. Interestingly, an increased number of circulating immature platelets represents an independent determinant of poor antiplatelet drug response in non-ET disorders at high CV risk^22^^[,27,28^.

Thus, the abnormal megakaryopoiesis that characterizes ET appears to account for a shorter duration of the antiplatelet effect of low-dose aspirin due to a faster renewal of platelet COX-1, an abnormality that could be rescued by shortening the aspirin dosing interval, but not by increasing the od dose^14,25^. Based on the two small, proof-of-concept studies^14,25^, bid low-dose aspirin is currently considered in the most recent treatment algorithm for low- to high-risk ET patients^1^. However, the clinical efficacy and safety of a bid low-dose aspirin regimen in ET remains to be investigated. Moreover, it should be considered that multiple daily dosing of any drug is usually associated with a lower patient’s compliance^29^. Although a bid low-dose aspirin regimen has been successfully tested in stroke patients^30^, nevertheless this issue should be addressed when proposing multiple daily drug intake for further clinical evaluation.

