### Part A

Patients will be randomized (1:1:1) in a double-blind fashion to aspirin 100 mg od (standard of care), 100 mg bid (i.e. breakfast and dinner), or 100 mg tid (i.e., breakfast, lunch, and dinner). Matching placebo will be used so that all patients will take active drug and placebo tablets tid. At randomization and after 2 weeks of study treatment, patients will undergo blood and urine sampling for serum TXB_2_ and urinary PGIM and TXM measurements at 8 a.m., immediately before aspirin dosing; thereafter, they will resume their open-label, standard aspirin regimen for the time interval necessary to assay serum and urine samples and analyze the data. The primary end points of part A will assess the biochemical efficacy, as reflected by the degree of suppression of serum TXB_2_ throughout the dosing interval, and biochemical safety, as assessed by urinary PGIM excretion, of the two experimental dosing regimens as compared to the standard regimen of aspirin administration. The secondary end point will assess their impact on in vivo platelet activation, as reflected by the urinary excretion of TXM.

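### The 80% power stated for aspirin tid versus bid does not hold under the planned ANOVA with Scheffe on untransformed serum TXB2, because the od variance is pooled into that contrast

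*Protocol article*

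**What the plan says.** All of this is in the protocol article, mainly under Study end points and statistical analysis.

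- **Expected values.** Serum TXB2 on od and bid is expected "to be 22 ± 33 and 5.0 ± 6.0 ng/ml, respectively". No mean or SD is given for tid.
- **Error rates.** "We plan to test with *α*-error of 0.05 and a *β*-error of 0.2 (power 80%) the following hypotheses". Two TXB2 hypotheses follow: bid against od, and "100 mg tid is superior to 100 mg bid, with a ≥50% reduction in serum TXB_2_ (required sample size 70 patients/arm".
- **Enrolment.** 70 per arm is raised to 100 for 30% dropout over the whole study. Part A allocates 1:1:1 to three arms.
- **Analysis.** "Differences in mean serum TXB_2_ values will be evaluated by one-way analysis of variance, using Scheffe multiple-comparison test", covering the three Part A treatments. Covariance analysis is added only if listed baseline factors differ between arms, and baseline TXB2 is not on that list. Neither a transformation nor an unequal-variance version is mentioned.
- **Choice of regimen (Part B section).** "The experimental aspirin regimen associated with a significantly lower serum TXB_2_ level and non-inferior urinary PGIM excretion rate" relative to od goes forward.

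**The concern.** The sizing and the named test use different variances. The sizing of tid versus bid makes sense only with the spread of those two arms. The analysis estimates one common variance from all three arms, and the od arm is expected to be more than five times as variable as bid (33 against 6.0). One of the two TXB2 hypotheses that set the sample size would then almost certainly be non-significant even if tid truly halves TXB2. In a dose-finding trial, that result could be read as showing that a third daily dose adds nothing, when the test could not have shown otherwise.

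**Working it through.** **Inputs.** From the article: od SD 33; bid 5.0 ± 6.0; alpha 0.05 with sidedness not stated; power 80%; n = 70 per arm, or 100 with no dropout (70/0.7 = 100). A 50% reduction takes 5.0 to 2.5 ng/ml, a difference of 2.5. *Assumption:* the tid SD is not given, so 2, 3 and 6 are used (3 keeps the bid coefficient of variation; 6 keeps the bid SD).

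**Step 1: reproduce the 70 per arm.** Two-arm formula: n = (z_alpha + z_beta)² × (6² + SD_tid²) / 2.5².

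- Two-sided 0.05: 7.849 × 40/6.25 = 50.2 (SD 2); 7.849 × 45/6.25 = 56.5 (SD 3); 7.849 × 72/6.25 = 90.4 (SD 6).
- One-sided 0.05, SD 6: 6.183 × 72/6.25 = 71.2, so 72 per arm; power at 70 is 79.4%.
- Two-sided 0.025, SD 3: 69 per arm.

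Several routes therefore lead to about 70, and the article does not say which was used. All are stand-alone two-arm calculations, and none contains the od SD of 33.

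**Step 2: the smallest significant difference under the named test.** MSE = (33² + 6² + SD_tid²)/3. With SD_tid = 3 this is (1089 + 36 + 9)/3 = 378, of which od supplies 1089/1134 = 96%. Scheffe critical difference = sqrt(2 × F(0.95; 2, 3n − 3)) × sqrt(2 × MSE/n).

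| n per arm | multiplier | pooled SE | Scheffe critical difference | unadjusted pooled t |
|---|---|---|---|---|
| 70 | 2.466 | 3.29 | 8.10 | 6.48 |
| 100 | 2.460 | 2.75 | 6.76 | 5.41 |

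Varying the tid SD from 0 to 6 moves the Scheffe figures only between 8.07 and 8.20 (70 per arm) and between 6.74 and 6.84 (100 per arm). The planned difference is 2.5. Complete suppression on tid would give an expected difference of only 5.0, still below every threshold in the table.

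**Step 3: power.** For n = 70 and SD_tid = 6, the true SE of the difference is sqrt(72/70) = 1.014, and (8.20 − 2.5)/1.014 = 5.6 standard errors, so power is about 1e-8 under normality. Simulation (20,000 trials per scenario; normal, lognormal and gamma data) gives at most about 0.5% for Scheffe, reached with lognormal data at 100 per arm. The unadjusted pooled test stays under 4% (lognormal 1.5 to 3.6%, lower for the other shapes). The cause is therefore the pooled variance and not the Scheffe adjustment.

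**Step 4: sample size the named test would need.** With SD_tid = 3, n = [(2.449 × sqrt(2 × 378) + 0.8416 × sqrt(45))/2.5]² = [(67.34 + 5.65)/2.5]², about 853 per arm. Over tid SD 2 to 6 the range is 842 to 907.

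**Step 5: alternatives at 70 per arm, tid SD 2 to 6, over the three data shapes.**

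- Welch, tid versus bid, unadjusted: about 69 to 98%.
- Games-Howell, which controls multiplicity over the three pairs: about 54 to 94%. Both are lowest at tid SD 6.
- Scheffe on log TXB2, for tid SD 2, 3 and 6: 78%, 96% and over 99% with lognormal data, but 1%, 33% and over 99% with gamma data of the same means and SDs.

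**Step 6: contrasts with od.** At the expected means of 22 and 5.0, the raw Scheffe test of bid versus od has 98% power or more at 70 per arm under all three shapes.

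**The case against.** **The full protocol or SAP may specify a log transformation.** It may, and an article need not give every detail. But the article already names both the test and the quantity compared (means), and it sizes this contrast in ng/ml. The conflict is between two things it states. What stands is the limit: the claim covers untransformed values only. The conditional covariance analysis does not remove the problem either, since ordinary multiple regression also assumes one residual variance.

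**Tid versus bid is not a decision criterion.** This is largely right. Study objectives, Part A and Part B all compare the experimental regimens with od. A reader might infer that the low power would lead to the wrong regimen being chosen, since both could qualify against od and tid versus bid would be the obvious tie-break. The article never says that this test decides, so that reading is not supported. How to choose when both qualify is a separate question. The hypothesis is nevertheless one of only two for which a TXB2 sample size is given, so its stated power should be right.

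**The whole Part A analysis fails.** A reader might also infer this, but Step 6 shows otherwise at the expected means. That reassurance applies to the expected fall from 22 to 5.0. At the minimum 50% fall (22 to 11, assumed bid SD 16.5 or 6), raw Scheffe power against od is 67 to 93% at 70 per arm.

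**Conclusion.** The point holds for untransformed serum TXB2. The stated 80% power for tid versus bid at 70 per arm fits only a stand-alone two-arm calculation. Under the analysis named in the article it is at most about 0.5%, whether 70 or 100 per arm are analysed. This rests on the article's SDs for od and bid, a tid mean of 2.5 ng/ml taken from the hypothesis, and an assumed tid SD of 2 to 6. The conclusion does not depend on which SD in that range is true or on which of the three data shapes applies.

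The consequence is limited to this one sized hypothesis and the risk that a non-significant result is taken as no gain over bid. It should be corrected, but it does not undermine the comparisons with od. It would also go too far to conclude that a log scale by itself solves the problem: that depends on a data shape the article does not establish.

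**What to change.** In Study end points and statistical analysis, replace the pooled-variance Scheffe test on mean TXB2 with an unequal-variance procedure on means: Games-Howell if multiplicity over the three pairs is to be controlled, or Welch for tid versus bid. Then restate the power of tid versus bid for the test chosen, with the assumed tid SD and the sidedness. That restatement matters, because at 70 per arm neither procedure reaches 80% across the whole range: if the tid SD is as large as 6, Welch can fall to about 69% and Games-Howell to about 54%. At 100 per arm, Welch gives about 82 to 98% for a tid SD of 3 or 6.

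A log-scale analysis is an alternative only if there is evidence that TXB2 is close to lognormal. It also changes what is estimated, from a difference in means to a ratio of geometric means. Under lognormality, halving the mean corresponds to a ratio of 0.61, 0.50 or 0.30 for tid SD 2, 3 or 6.

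The cost is a change of variance estimate and a corrected power statement, made before unblinding. No extra patients, samples or data are needed.
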